#### 2.7.1 Primary outcome

##### 2.7.1.1 Numeric Rating Scale (NRS)

This instrument serves as a standardized tool for assessing lumbar pain intensity, utilizing a numerical rating system spanning from 0 (indicating complete absence of pain) to 10 (representing the maximum tolerable pain threshold) (11). For patients with chronic LBP, a 2-point difference on the NRS was defined as the minimal clinically important difference (MCID) (25). The NRS score at week 8 will be regarded as the primary outcome measure.

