### 2.10 Sample size calculation

The sample size calculation was performed using G*Power software (version 3.1.9.7; University of Düsseldorf, Germany). The calculation was based on a prior clinical trial evaluating acupuncture for CNLBP, which also used the NRS as the primary outcome measure (35). According to the reported data from that study, the post-treatment mean ± standard deviation (SD) was 2.96 ± 3.44 for the treatment group (*n* = 29) and 2.00 ± 2.79 for the control group (*n* = 28), yielding an effect size of 0.3 (Cohen’s d), suggesting a small intervention effect. Considering subjective feedback from CNLBP patients who had previously received moxibustion therapy regarding its perceived efficacy, we estimated a potential effect size of 0.5 (moderate effect) for moxibustion treatment. With α set at 0.05, power (1-β) at 0.80, and these parameters entered into G*Power, the calculation indicated a required sample size of 64 participants per group. Accounting for an expected 15% dropout rate during the trial, the total sample size was adjusted to 150 participants (75 per group).

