### 2.11 Statistical analysis

To minimize potential biases arising from manual intervention, the statistical analyses for this study will be conducted independently by two blinded statisticians using SPSS (version 25), both of whom will be unaware of the group assignments and treatment details. Data analysis will adhere to the intention-to-treat principle. Participants who complete the baseline assessment of the primary outcome and receive at least one session of moxibustion or sham moxibustion treatment will be included in the ITT analysis. Continuous variables will be presented as mean ± standard deviation (SD) or median (P25-P75), with statistical comparisons performed using Student’s *t*-test or non-parametric Mann-Whitney U test as appropriate. Categorical variables will be described as frequencies and percentages, with between-group differences analyzed via χ^2^ test or Fisher’s exact test. It should be noted that all baseline comparisons serve solely to verify inter-group balance after randomization, and their results will not be used to adjust the primary analysis model. For repeatedly measured outcome variables, a random-intercept mixed-effects model (MMRM) will be employed. Specifically, the model will include observed values at each scheduled assessment timepoint (weeks 4, 8, and 16) as dependent variables, with baseline values incorporated as fixed-effect covariates. Treatment group (moxibustion vs. sham moxibustion), timepoint (weeks 4, 8, and 16), and their interaction will be modeled as fixed-effect categorical variables. Additionally, individual subject intercepts will be included as random effects. Between-group comparisons at each timepoint will be estimated through least squares mean differences derived from treatment-by-time interaction terms, with corresponding *P*-values and 95% confidence intervals (CI) reported. All statistical tests will be two-sided, and a *P*-value < 0.05 will be considered statistically significant.

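### One baseline slope for weeks 4, 8 and 16: valid, and harmless for the week-8 primary, but a baseline-by-timepoint term would cheaply protect the week-4 and week-16 contrasts

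*Protocol article*

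**What the plan says.** Section 2.11 (Statistical analysis) sets out the model for repeatedly measured outcomes term by term. The dependent variable is the observed value at weeks 4, 8 and 16, "with baseline values incorporated as fixed-effect covariates". The remaining fixed effects are "Treatment group (moxibustion vs. sham moxibustion), timepoint (weeks 4, 8, and 16), and their interaction will be modeled as fixed-effect categorical variables". For the covariance, "individual subject intercepts will be included as random effects". Section 2.11 then states: "Between-group comparisons at each timepoint will be estimated through least squares mean differences derived from treatment-by-time interaction terms", and a P-value and 95% confidence interval are to be reported for each.

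The interaction named is between group and timepoint. No product of baseline and timepoint appears, so the model as described has one baseline slope for all three visits.

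Section 2.7.1.1 fixes the primary timepoint: "The NRS score at week 8 will be regarded as the primary outcome measure". Table 1 schedules NRS, ODI, FABQ and SF-36 at all four assessments, so the same model produces week-4 and week-16 contrasts for each of them.

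**The concern.** The three post-baseline visits differ in kind: mid-treatment, end of treatment, and 8 weeks after treatment ends. A baseline score may predict week 4 better than week 16. If so, one averaged slope adjusts too little at week 4 and too much at week 16, and each of those contrasts is less precise than it could be.

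There is also a possible bias. If those still observed at week 16 differ in baseline between the arms, and the slope used is wrong for week 16, the adjustment leaves part of that difference in the treatment contrast. Week 16 is the only assessment after treatment has stopped, so it carries all the evidence on whether an effect lasts.

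**Working it through.** **The plan's own figure.** Section 2.10 gives 64 per group, from an effect size of 0.5, "With α set at 0.05" and "power (1-β) at 0.80"; section 2.11 adds "All statistical tests will be two-sided". A two-sample t-test with the noncentral t distribution gives power 0.801 at 64 per group, so the figure reproduces. With 15% dropout, 128/0.85 = 150.6, against 150 stated. This calculation does not use the baseline term, so the point below does not touch it.

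**Precision, complete data.** Assumptions, none of them in the article: equal SDs, and correlations ρ_t between baseline and the score at visit t. With a random intercept and no missing visits, the common slope b is the mean of the three ρ_t. In units of the outcome variance, the residual variance is 1 − 2bρ_t + b² with one slope and 1 − ρ_t² with a slope per visit. SE inflation is the square root of their ratio, minus 1.

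| Assumed ρ at weeks 4/8/16 | b | Week 4 | Week 8 | Week 16 |
|---|---|---|---|---|
| 0.6/0.5/0.4 | 0.500 | √(0.65/0.64): 0.8% | 0% | √(0.85/0.84): 0.6% |
| 0.7/0.5/0.3 | 0.500 | √(0.55/0.51): 3.8% | 0% | √(0.95/0.91): 2.2% |
| 0.7/0.4/0.3 | 0.467 | √(0.5644/0.51): 5.2% | √(0.8444/0.84): 0.3% | √(0.9378/0.91): 1.5% |

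If the three correlations are equal, the loss is zero at every visit.

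These are sampling SEs. A random-intercept model pools one variance over visits, so the SE it reports moves less. For 0.6/0.5/0.4 the average variances are 0.75 and (0.64 + 0.75 + 0.84)/3 = 0.743, so the reported SE is 0.4% larger with one slope. For 0.7/0.5/0.3 they are 0.75 and (0.51 + 0.75 + 0.91)/3 = 0.723, a difference of 1.8%.

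**Bias under dropout.** This was checked by simulating 1,500 trials of 150 participants per scenario with a true group difference of zero. Assumptions: follow-up NRS SD 2.0, correlations among follow-up scores 0.65 and 0.50, and about 14 to 16% lost by week 16 (40% of it before week 8). Week-16 bias of the one-slope model, in NRS points, with the SD equivalent (divided by 2.0) in brackets:

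| Assumed ρ at weeks 4/8/16 | Same dependence in both arms | One arm only | Opposite in the arms |
|---|---|---|---|
| 0.5/0.5/0.5 | 0.005 | 0.002 | 0.005 |
| 0.5/0.4/0.3 | 0.005 | 0.034 (0.017) | 0.069 (0.035) |
| 0.6/0.45/0.3 | 0.005 | 0.049 (0.025) | 0.100 (0.050) |
| 0.7/0.45/0.2 (extreme) | 0.005 | 0.080 (0.040) | 0.163 (0.082) |

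The Monte Carlo error is 0.008 to 0.009, so the first row and the first results column are zero within error. Very strong opposite dependence raised the last column to between 0.116 and 0.278 points in the three declining sets. With baseline by timepoint added, week-16 bias was at most 0.005 in every scenario. For scale, in the 0.6/0.45/0.3 set the week-16 bias was 0.15 of an SE with one-arm dependence and 0.30 with opposite dependence.

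At week 8 the largest bias in this simulation was 0.037 points (0.019 SD). Correlations such as 0.7/0.4/0.3, where week 8 lies off the mean slope, can bring it to about 0.03 SD.

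**The case against.** The strongest reply is that a common baseline slope is a valid and widely used adjustment in a randomised trial, that nothing in the article is contradicted, and that crossing baseline with visit is a detail often left to an analysis plan, which is not shown. The first two parts stand. The third stands only in part: section 2.11 does not leave the terms open but names them, including the one interaction it wants. The full plan may still contain the term.

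A second reply also stands. The article gives no correlation between baseline and follow-up and no dropout pattern, only 15% overall, so a weakening slope and arm-specific dropout are both assumptions.

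Three stronger readings are tempting and are not supported:
- A reader might infer that dropout related to baseline is enough to bias week 16. It is not. With the same dependence in both arms the misfit cancels. Bias needs a slope that changes by visit together with dropout whose relation to baseline differs by arm.
- A reader might infer that the primary result is at risk. Week 8 is the middle visit, and its slope usually lies close to the average one.
- A reader might infer a material loss of power. For scale, at 64 per group and an effect size of 0.5, a 1.6% rise in variance costs about 0.6 percentage points of power.

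**Conclusion.** The point holds as a minor improvement, not as an error. The described model uses one baseline slope at all visits. The primary week-8 contrast is essentially unaffected (SE loss 0 to 0.3%, bias at most about 0.03 SD).

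At weeks 4 and 16 the cost depends on a slope that changes over time: under 1% of the SE for a gentle decline, and up to about 5% at week 4 and 2% at week 16 for a steep one. If dropout also depends on baseline differently by arm, with about 15% lost by week 16, week-16 bias is roughly 0.01 to 0.03 SD (one arm; 0.04 in the extreme set) or 0.03 to 0.08 SD (opposite directions). At the assumed SD of 2.0, 0.08 SD is 0.16 NRS points, against the 2-point MCID in section 2.7.1.1. Direction and order of size can be relied on; the exact figures rest on assumed SDs, correlations and dropout.

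**What to change.** In section 2.11, add baseline by timepoint as a fixed effect in the mixed model for NRS, ODI, FABQ and SF-36, and estimate the group difference at each visit from that model. The cost is one model term, two degrees of freedom and no new data. If the slope is in fact constant, the loss of precision is negligible. Make the change before the data are unblinded, so that it cannot look data-driven. If the full analysis plan already has the term, aligning the article with it is enough.

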## 2 Methods

### 2.1 Trial design

This is a multicenter, single - blind, randomized controlled trial in which 150 eligible participants will undergo 1:1 randomization to receive either verum moxibustion therapy or a sham control procedure. This study will span a total duration of 16 weeks, comprising an 8-week therapeutic intervention phase followed by an 8-week follow-up period.

This trial has been registered on the International Traditional Medicine Clinical Trial Registry (ITMCTR2025001296). This study protocol adheres to the SPIRIT reporting guidelines (21). The SPIRIT checklist of this trial is given in Supplementary material. The flow diagram of this trial is illustrated in Figure 1, while the comprehensive schedule for the study is outlined in Table 1.

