### 2.4 Randomization

The study will employ a permuted block randomization method (with block size set to 4) stratified by research center for sequential allocation of participants. The randomization sequence will be generated by a statistician independent of the study team using SAS software (version 9.4; SAS Institute Inc., Cary, NC, USA). Research personnel will have no access to the randomization sequence. Randomization numbers will be sealed in sequentially numbered opaque envelopes and stored in a double-locked cabinet. Following completion of baseline assessments and submission of informed consent forms, envelopes will be opened in sequential order of enrollment to reveal group assignments. The allocation sequence will remain concealed such that the next participant’s assignment cannot be predicted in advance.

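### Randomisation is stratified by centre but the mixed model has no centre term; if centre predicts week-8 NRS, the primary analysis is slightly conservative and some precision is forgone.

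*Protocol article*

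**What the plan says.** Protocol article, section 2.4 (Randomization) allocates participants by a "permuted block randomization method (with block size set to 4) stratified by research center". Section 2.2 gives three hospitals, and section 2.1 states that "150 eligible participants will undergo 1:1 randomization". Centre is the only stratification factor named.

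Section 2.11 (Statistical analysis) specifies the model for repeatedly measured outcomes in full. The observed values at weeks 4, 8 and 16 are the response, the baseline value is a covariate, "Treatment group (moxibustion vs. sham moxibustion), timepoint (weeks 4, 8, and 16), and their interaction will be modeled as fixed-effect categorical variables", and each subject has a random intercept. The week-8 treatment difference, which is the primary comparison, comes from the group-by-time term. No other section adds centre to this model or explains its absence.

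Section 2.11 also says that results of baseline comparisons will not be used to adjust the primary model. That rules out choosing covariates from observed imbalance. It does not address a factor fixed in advance by the design.

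**The concern.** Blocking within centre makes the arms nearly equal in size at each hospital, so differences between hospitals largely cancel from the treatment contrast. A model without centre does not recognise this: it leaves the between-centre variance in the variance from which the standard error is computed. Design and analysis then do not match. The reported interval is wider than the design warrants, and the test rejects less often than its nominal level.

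The random subject intercept does not repair this. It absorbs centre differences into the between-subject variance, and that variance stays in the standard error of a between-subject contrast.

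What is at stake is precision: the part that stratification could have gained is not used.

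**Working it through.** **Inputs from the documents.** Section 2.10: "With α set at 0.05, power (1-β) at 0.80"; "we estimated a potential effect size of 0.5 (moderate effect) for moxibustion treatment"; "the calculation indicated a required sample size of 64 participants per group"; 15% dropout; 150 in total. Section 2.11: "All statistical tests will be two-sided".

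**Inputs assumed.** rho, the share of week-8 NRS residual variance (after baseline adjustment) that lies between centres: 0.02, 0.05 and 0.10. r, the correlation of baseline with week-8 NRS: 0.5, with 0.3 and 0.6 as a range. The documents give neither.

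**Step 1: the plan's own figure.** A two-sided two-sample t-test with d = 0.5 and alpha 0.05 has 80.1% power at 64 per group (noncentral t), so 64 reproduces. For dropout, 128/0.85 = 150.6; the stated 150 agrees within rounding. This calculation uses neither centre nor baseline.

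**Step 2: standard error.** With allocation balanced within centres, the true variance of the contrast is proportional to 1 − rho. Without a centre term the reported variance is proportional to 1. The ratio of reported to true SE is 1/sqrt(1 − rho):
- rho 0.02: 1/sqrt(0.98) = 1.010
- rho 0.05: 1/sqrt(0.95) = 1.026
- rho 0.10: 1/sqrt(0.90) = 1.054

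**Step 3: type I error.** Actual alpha = 2 × [1 − Phi(1.96/sqrt(1 − rho))] = 0.0477, 0.0443 and 0.0388.

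**Step 4: power, d = 0.5 on the residual SD.** Let k = d/sqrt(2/64) = 0.5/0.1768 = 2.828. Power without centre is Phi[(k − 1.96)/sqrt(1 − rho)]; with centre it is Phi[k/sqrt(1 − rho) − 1.96].

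| rho | without centre | with centre | points forgone |
|---|---|---|---|
| 0 | 80.7% | 80.7% | 0 |
| 0.02 | 81.0% | 81.5% | 0.5 |
| 0.05 | 81.4% | 82.7% | 1.3 |
| 0.10 | 82.0% | 84.6% | 2.6 |

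The normal approximation gives 80.7% at rho 0, where the t-test gives 80.1%.

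**Step 5: power, d = 0.5 on the raw SD.** The model already contains baseline. With r = 0.5 the effect in residual SD units is 0.5/sqrt(1 − 0.25) = 0.577, so k = 0.577/0.1768 = 3.266.

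| rho | without centre | with centre | points forgone |
|---|---|---|---|
| 0.02 | 90.6% | 91.0% | 0.3 |
| 0.05 | 91.0% | 91.8% | 0.8 |
| 0.10 | 91.6% | 93.1% | 1.5 |

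With r = 0.3 the losses are 0.5, 1.2 and 2.3 points; with r = 0.6 they are 0.2, 0.5 and 1.0.

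**Step 6: simulation check of direction.** A week-8 ANCOVA was simulated with three centres of 50, blocks of 4, 15% dropout, baseline correlation 0.5 and 6,000 replicates per scenario. Here the centre share was set on the raw variance. A raw share of 0.10 is a residual share of 0.10/(0.10 + 0.90 × 0.75) = 0.129, so the results are not on the scale of the tables. The mean SE was 0.1565 without centre and 0.1462 with it, a ratio of 1.070, against 1/sqrt(1 − 0.129) = 1.071 from the formula. Type I error was 0.041 without centre and 0.052 with it. Power at a difference of 0.45 was 82.6% and 86.0%. With no centre effect, type I error was 0.050 for both models.

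**The case against.** Several points on the other side stand.

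- **The consequence is conditional.** If centre does not predict week-8 NRS after baseline adjustment, nothing is lost (rho = 0 above). The documents give no centre variance, so the omission is certain but its effect is not. A reader might infer that the primary interval is certainly too wide; the documents do not support that.
- **It is not a shortfall against the design.** In every scenario in the two power tables, power without centre is above the planned 80%. What is lost is extra power that adjustment would have given.
- **The formula is an idealisation.** Last blocks may be incomplete, dropout is expected, and section 2.11 limits the analysis to participants with a baseline value and at least one session. Balance within centres is therefore only approximate among those analysed. The simulation includes incomplete blocks and dropout and still shows the same direction.
- **The reach is limited.** GPE is measured once, and fNIRS only at baseline and week 8. Section 2.11 states no regression model for them, so there is nothing to which centre could be added. Extending the point to all secondary outcomes goes too far.

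A reader might also infer bias, excess false positives or an invalid sample size. None follows: the error is conservative, the balanced contrast is not shifted, and the 64 per group came from an unadjusted t-test.

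One defence stands only in part. This is a condensed article, and an analysis plan not shown here might include centre. But the article does not leave the model open; it fixes the fixed and random effects one by one, so adding centre later would depart from the published model.

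**Conclusion.** The point holds as a conditional and modest one. The trial randomises within centre and specifies a model that ignores centre. If centres account for 2% to 10% of the residual variance, the SE is overstated by about 1% to 5%, and the nominal 5% test runs at about 4.8% to 3.9%. The power forgone is roughly 0.5 to 2.6 points with d = 0.5 on the residual SD, or 0.3 to 1.5 points with d = 0.5 on the raw SD and a baseline correlation of 0.5. These figures rest on assumed values of rho and r, near-balance within centres, 64 evaluable participants per arm, and a single week-8 comparison in place of the full repeated-measures model. The validity of the planned test is not in question.

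**What to change.** In section 2.11, add research centre (three levels) as a fixed effect to the repeated-measures mixed model for the primary NRS outcome, and to the same model for ODI, FABQ and SF-36. State that centre is included because randomisation is stratified by it, so that it is not confused with covariates chosen from baseline comparisons. The cost is one line of text, settled before unblinding, and two degrees of freedom. It needs no further data or participants and no change to the sample size. If centre proves not to be prognostic, the loss is negligible: in the simulation without a centre effect the mean SE was 0.1540 with centre and 0.1538 without.

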## 3 Discussion

Chronic non-specific low back pain has been emerging as a leading cause of population-based disability worldwide for decades (36). Current guidelines recommend physical therapy as a first-line treatment for CNLBP. However, patients do not always derive sufficient benefits from physical therapy alone. Coupled with the potential adverse effects and addiction risks associated with pharmacological interventions, there is a growing demand for safer and more effective therapeutic options for CNLBP (37). Moxibustion, a key component of TCM, has contributed to the health of the Chinese population for thousands of years. Clinical observations suggest that moxibustion can alleviate pain and somatic dysfunction in patients with CNLBP to some extent, positioning it as a promising complementary therapeutic approach. Nevertheless, rigorously conducted clinical trials and robust evidence supporting moxibustion for CNLBP remain scarce, and the precise mechanism of action underlying moxibustion remains incompletely elucidated. Therefore, we conducted this meticulously designed multicenter, single-blind randomized controlled trial to validate the efficacy of moxibustion in patients with CNLBP.

According to TCM theory, acupoints exhibit local therapeutic effects, meaning each acupoint located at a specific anatomical position can treat diseases in its vicinity and adjacent tissues and organs. These acupoints, termed “local acupoints”, are commonly used for managing musculoskeletal disorders and somatic pain conditions (38). In this trial, we selected Shenshu (BL23), Yaoyangguan (GV3), and Jinsuo (GV8), all situated in the lumbosacral region and frequently utilized in clinical acupuncture practice for chronic LBP (38, 39). Unlike sole reliance on herbal pharmacotherapy, the therapeutic effects of moxibustion arise from the dynamic interaction between local physical stimulation and the body’s intrinsic regulatory systems. This mechanism embodies the distinctive therapeutic philosophy underlying TCM approaches to disease management. Due to the inherent methodological challenges posed by the well-documented placebo effect in TCM complementary therapies, the implementation of a credible sham moxibustion control condition became an essential component of the study design. It is well-established that temperature is a pivotal factor influencing the therapeutic outcomes of moxibustion treatment. This is because when there is effective heat insulation, the clinical benefits derived from moxibustion are markedly diminished. In the current study, the sham moxibustion intervention was applied at a distance of 8–10 cm with temperature maintained at 37 ± 1 °C. This protocol minimized thermal stimulation while allowing participants to perceive the characteristic odor of burning moxa, thereby achieving effective blinding (40, 41).

Pain is the predominant symptom of CNLBP. Consequently, the NRS was adopted to evaluate whether the intervention could alleviate patients’ pain intensity. For individuals with CNLBP, psychological factors serve as critical predictors of long-term disability, with fear of pain often contributing more to functional limitations than the pain itself (42, 43). Fear-avoidance beliefs may drive patients to adopt protective behaviors, thereby precipitating and perpetuating disability while hindering the restoration of normal functional capacity (44, 45). Therefore, the FABQ and the ODI were employed to assess whether the intervention could ameliorate pain-related fear and associated physical dysfunction. Given that persistent pain severely compromises patients’ physical and mental wellbeing, the SF-36 was additionally utilized to comprehensively evaluate whether the intervention could enhance patients’ quality of daily life.

The ambiguous action mechanism of moxibustion therapy stands as one of the crucial factors restricting its global promotion and application. As is widely acknowledged, the experience of pain extends beyond localized pathological alterations at the site of injury to encompass the neural processing within cortical regions mediating pain perception. Thus, it is highly worthwhile to investigate whether the mechanism by which moxibustion alleviates pain is linked to its ability to regulate the functional activity of pain-related areas in the cerebral cortex. Previous studies have demonstrated that CNLBP induces structural and functional alterations in brain regions associated with pain modulation and postural control, with impaired postural control potentially contributing to the persistence and recurrence of pain in CNLBP patients (46, 47). In this study, we selected bilateral DLPFC, M1, S1, SMA, and PMC as regions of interest, as these cortical areas play critical roles in human pain modulation and postural control (48, 49). fNIRS will be employed to compare activation patterns of these cortical regions in participants before and after intervention, which will help elucidate the potential neurophysiological mechanisms underlying moxibustion therapy for CNLBP.

However, limitations exist in this trial. Firstly, owing to the unique characteristic of moxibustion therapy, achieving true blinding for clinical practitioners remains challenging, which may introduce potential performance bias. Independent assessment of outcome measures will help resolve this issue. Secondly, participants’ high expectations regarding the efficacy of moxibustion may introduce bias into the outcomes.

This trial may have some significant implications. To begin with, this study aims to comprehensively assess the diverse impacts that moxibustion exerts on pain severity, physical functional impairment, pain-related fear, and the overall quality of life among patients suffering from CNLBP. If the results support our hypotheses, moxibustion therapy could be widely implemented in future clinical practice. Secondly, this study will investigate whether therapeutic efficacy of moxibustion for CNLBP varies with temperature parameters, which will provide data-driven evidence to optimize treatment protocols. Lastly, fNIRS will be employed in this study to investigate cortical activation patterns in patients with CNLBP, thereby elucidating the neurobiological mechanisms underlying moxibustion’s therapeutic effects from a modern scientific perspective. In summary, this study may provide a complementary therapeutic strategy for CNLBP management and may promote further research on moxibustion treatment in the future.

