**Discussion:**

The results obtained from this research are expected to indicate that moxibustion therapy can function as a highly efficacious treatment approach for managing CNLBP. Additionally, this trial will employ fNIRS technology to investigate the activation characteristics of pain-related cortical regions in the brains of CNLBP patients before and after moxibustion treatment. This will contribute to elucidating the underlying mechanisms of moxibustion.

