### 2.7 Outcome measures

The assessment of outcomes encompasses the following domains: low back pain intensity, somatic dysfunction, pain-related fear and avoidance behaviors, health status, and cerebral cortex activation characteristics. Assessments will be performed at baseline, mid-intervention (week 4), post-intervention (week 8), and follow-up (week 16). It is worth mentioning that participants will be required to rate the overall efficacy of the received intervention using the Global Perceived Effect (GPE), at week 8 (post-intervention). Additionally, functional near-infrared spectroscopy (fNIRS) will be employed by the researchers to assess cerebral cortex activation characteristics in each group at baseline and week 8 (end of intervention).

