##### 2.7.2.5 fNIRS

Pain is closely associated with the functional connectivity of relevant cerebral cortical regions. fNIRS is an emerging optical imaging technique that reflects cortical activation patterns associated with neuronal activity by detecting concentration changes in oxygenated hemoglobin (HbO_2_) within localized cerebral regions (34). fNIRS examinations will be conducted in a quiet room with subdued lighting. Data acquisition will be performed using a 48-channel near-infrared optical imaging system (NirScan-6000A, HuiChuang Medical Equipment Co., Ltd., Danyang, China). This system operates at two wavelengths (730 nm, and 850 nm) with a sampling rate of 11 Hz. It comprises 15 light source optodes and 16 photodetector probes, with an optode-to-detector distance of 3 cm. Light sources and detectors will be symmetrically distributed over the bilateral dorsolateral prefrontal cortex (DLPFC), primary motor cortex (M1), primary somatosensory cortex (S1), premotor cortex (PMC), and supplementary motor area (SMA) in accordance with the international 10-20 standard electrode placement system. Acquired data will be analyzed using the NirSpark software.

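### The fNIRS mechanism question is framed as before versus after rather than moxibustion versus sham, and the only stated test that fits its schedule discards the baseline scan

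*Protocol article*

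**What the plan says.** **The question.** Section 3 says that "fNIRS will be employed to compare activation patterns of these cortical regions in participants before and after intervention", and that this will help to explain how moxibustion acts. The Discussion paragraph of the abstract has the same framing: the trial will study "activation characteristics of pain-related cortical regions in the brains of CNLBP patients before and after moxibustion treatment". The closing part of section 3 goes further and expects the fNIRS results to show the neurobiological basis of the treatment effect. None of these places mentions the sham arm.

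**The data.** Section 2.7 has fNIRS used "to assess cerebral cortex activation characteristics in each group at baseline and week 8 (end of intervention"). Table 1 agrees: two scans, at weeks 0 and 8. Section 3 names five bilateral regions of interest (DLPFC, M1, S1, SMA, PMC).

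**The analysis.** Section 2.11 has no rule specific to fNIRS. It states: "For repeatedly measured outcome variables, a random-intercept mixed-effects model (MMRM) will be employed". In that model the dependent variables are "observed values at each scheduled assessment timepoint (weeks 4, 8, and 16) as dependent variables", with the baseline value as a covariate. The same section gives a Student's t-test or Mann-Whitney U test for continuous variables, and one two-sided threshold of P < 0.05 for every test, with no adjustment for multiple tests.

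**The concern.** Randomisation protects the comparison between arms, not the change within one. A patient's cortical response may shift between two scans because of expectation, natural fluctuation of the pain, or familiarity with the scan. The article itself acknowledges the first of these: section 3 justifies the sham arm by the placebo response to such therapies and lists high patient expectations as a limitation. If the before-after comparison is carried out as worded, non-specific change will be credited to moxibustion.

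The statistical section does not settle the matter. Its baseline-adjusted model is written for outcomes with three post-baseline visits, and what is left for fNIRS makes no use of the baseline scan. Several regions, each tested at 0.05, then add some inflation of the false-positive rate.

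**Working it through.** The article states no figure for the fNIRS tests, so there is none to reproduce. Its only sample-size figure serves the pain score and is used here as the number scanned. A two-sided t-test with d = 0.5, alpha 0.05 and power 0.80 gives 63.8, so 64 per group as stated in section 2.10; 75 × 0.85 = 63.75 also leaves about 64 after dropout.

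**1. Before-after test when moxibustion has no specific effect**

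Let both arms share a non-specific change of δ standard deviations of the within-patient change. δ is assumed; the article gives no fNIRS variability. The paired t-test in one arm has 63 degrees of freedom and noncentrality δ√64 = 8δ.

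| δ (assumed) | Noncentrality | Moxibustion arm significant | Moxibustion arm significant, sham arm not |
|---|---|---|---|
| 0.2 | 1.6 | 35% | 0.351 × 0.649 = 23% |
| 0.3 | 2.4 | 66% | 0.657 × 0.343 = 23% |
| 0.5 | 4.0 | 98% | 0.976 × 0.024 = 2% |

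The last column shows that setting two within-arm P-values side by side does not replace a direct contrast. A valid between-arm test would be significant in 5% of trials in every row.

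**2. Fit of the stated model**

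NRS, ODI, FABQ and SF-36 are measured at weeks 4, 8 and 16. fNIRS is measured after baseline only at week 8. With one post-baseline value the time factor has a single level, and a random intercept cannot be separated from the residual. Without those terms the model reduces to ANCOVA on the baseline value, but section 2.11 does not say so.

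**3. Cost of discarding the baseline scan**

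Compared with a test on week-8 values alone, ANCOVA multiplies the variance of the arm difference by 1 − r², where r is the correlation between baseline and week 8 (assumed).

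- r = 0.3: 1 − 0.09 = 0.91, a 9% reduction
- r = 0.7: 1 − 0.49 = 0.51, a 49% reduction

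**4. Several regions at 0.05 each**

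For k independent tests the chance of at least one false positive is 1 − 0.95^k. The correlated cases were simulated with equally correlated normal statistics; the correlations are assumed.

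| Tests | Independent | Correlation 0.7 | Correlation 0.9 |
|---|---|---|---|
| 5 (sides pooled) | 1 − 0.95^5 = 22.6% | 15% | 10% |
| 10 (sides separate) | 1 − 0.95^10 = 40.1% | 22% | 13% |

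**The case against.** The before-after wording stands in the Discussion and the abstract, not in an analysis specification. Section 2.7 shows that both arms are scanned, and section 2.11 names no paired test. Its generic t-test or Mann-Whitney test, applied to week-8 values, is a valid randomised comparison, so omitting the baseline scan costs precision, not validity. The mechanism work is called preliminary, fNIRS is a secondary outcome, and details of imaging endpoints are often left to an analysis plan that is not shown here.

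Much of this stands. A between-arm comparison is not excluded, and the absence of imaging detail is not the complaint. What the objection does not answer is that every place where the article states the fNIRS question states it as before versus after, and draws a conclusion about moxibustion from it.

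Three stronger readings are tempting and are not supported:

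- **Testing over 48 channels.** Section 2.7.2.5 says "Data acquisition will be performed using a 48-channel near-infrared optical imaging system". That describes the device. No section makes the channel the unit of testing, and section 3 names regions. The figure 1 − 0.95^48 = 91% therefore belongs to an analysis that the article does not propose.
- **A contradiction between model and schedule.** The mixed model is limited to repeatedly measured outcomes, so fNIRS simply falls outside it. This is a gap in coverage.
- **False mechanism claims are likely.** From multiple testing alone, the region-level risk is 10% to 40%: above 5%, but below one half.

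**Conclusion.** The point holds for the framing and for the test that is left over. As published, the fNIRS question would attribute to moxibustion a change that the sham arm was included to separate out. How often this misleads depends on the size of the non-specific change, which the article does not give: 35% to 98% of trials for an assumed 0.2 to 0.5 SD with 64 scanned per arm. The direction of the problem does not depend on that assumption.

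Using the generic two-sample test instead would be valid but would give up a 9% to 49% reduction in variance at assumed correlations of 0.3 to 0.7. The multiplicity point is secondary, and its size depends on whether sides are pooled and on the correlation between regions.

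The primary pain outcome and the sample size are not affected. The change should be made before analysis because explaining the mechanism is a stated aim, but it concerns a secondary outcome described as preliminary.

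**What to change.** 1. In section 2.11, or in the analysis plan, state the fNIRS test as the moxibustion-minus-sham difference at week 8 for the named regions, by ANCOVA with the baseline fNIRS value and centre as covariates. Centre is the stratification factor in section 2.4, and baseline adjustment matches what the plan already does for the other scales.
2. Report before-after changes within each arm as descriptive only.
3. State whether the two sides are pooled. Then either control the false discovery rate across regions (for example Benjamini-Hochberg at 5%) or label the region results exploratory.
4. Align the abstract and both places in section 3 with the between-arm contrast.

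No new visits, scans or patients are needed. The cost is that fewer regions will be called significant. As a conservative guide, Bonferroni with 64 per arm, d = 0.5 and no baseline adjustment gives power of 59% over 5 tests (alpha 0.05/5 = 0.01) and 49% over 10 (alpha 0.05/10 = 0.005), against 80% for one uncorrected test. False discovery rate control is less strict than this, and baseline adjustment recovers some of the loss.
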